### Data management

The principal data source for the this study are pseudonymised routinely collected care data extracted from general practices of the RCGP RSC network’s database; there are over 500 general practices in this network. All general practices in the UK use an EHR to maintain patient medical records. Data are entered into a patient’s computerised medical system as coded data or free text. The RCGP RSC extract only coded data, that is, where the clinician codes a disease or symptom into their EHR system.^27^

The RCGP RSC has no role in updating clinical data recorded by clinicians as part of their consultation and care. However, the RCGP RSC practices do received focused feedback about data quality around its surveillance function, influenza other infections, vaccine update and effectiveness. This is done via team of PLOs and a dashboard.^28 29^

RCGP RSC maintains an auditable trail for all the stages of data processing to ensure the quality of data are not compromised by the processing. For example, checking the prevalence of certain conditions and outliers revealed by the data is consistent with those reported in the literature. The standard operating procedures for data extraction and data processing, and data access are available from https://clininf.eu/index.php/information-governance/

### Discontinuations and withdrawals from the study

Each practice has the right to withdraw from the study at any time. Data from withdrawn practices will be included in analyses up to the point of withdrawal, unless they indicate that they wish to withdraw previously collected data from analysis.

### Sample size

Practice lists sizes within the RCGP RSC are approximately 10 000. In England, diagnosis rate of new cancer was 523/100 000 per year (2014/2015).^30^ Therefore, we could expect 53 new cancers per year per practice. Therefore, in each 2-month step, there would be 8–9 cancers per cluster.

The median primary care interval between first presentation and specialist referral^22 31^ is 5 days, IQR of 0–27.^32^ Some cancers present with clear red flag symptoms leading to immediate specialist referral. Presentations of vague symptoms such as weight loss are less likely to be immediately referred and may benefit from using the safety-netting template. This symptom is associated with several cancers such as prostate, colorectal, lung, gastro-oesophageal and pancreatic.^33^ The median primary care interval for lung cancer is 14 days (IQR 2–45).^32^ Using Stata V.14 to conduct the sample size calculations we showed that with the design in figure 1 and 60 practices we would be able to detect an effect size of 2 days with 80% power.

Currently, approximately 19% of cancers are diagnosed following an emergency presentation.^34^ With nine cancers per step per cluster we would be powered to detect a difference of 5%.

Under another scenario of considering primary care intervals towards the 90th centile of 60 days, with 60 practices, entering the stepped wedge design in six steps we would be able to detect a minimal difference of 13 days. However, if we consider that these patients with longer delays are in the 90th centile, then instead of expected cancers per cluster per step of 9—there would be around 1. This would allow us to detect a minimal difference of between 9 and 39 days dependent on the assumption of the distribution of the primary care delays.

Several scenarios are shown in table 3, all based on 60 practices, entering in six blocks, with a 12-month preintervention period. In summary, our main analysis will focus on all cancers, but we can conduct prespecified subgroup analyses restricting to cancers that typically have longer delays.

**Table 3 T3:** Scenarios for various assumptions used in the sample size calculations

Assumptions	All cancers (based on lung cancer)	All cancers	All cancers	All cancers	Restricting to only 90^th^ centile delays	Restricting to only 90th centile delays
Median (days)	14	14	60	60	60	60
Range (days)	0–60	0–100	0–365	0–100	14–100	14–365
N of cancers per step per cluster	9	9	9	9	1	1
Minimum detectable difference (days)	2	5	13	4	9	39
Notes		Allowing greater range		Lower upper value for Primary Care Interval	Minimum set to median of all cancers	Min set to median of all cancers, but increased upper range

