## Methods and analyses

### Outcomes and outcome definitions

#### Primary outcome: primary care interval for cancer diagnoses

The primary care interval is defined as the number of days between the first recorded symptoms of cancer (within the year prior to diagnosis) and subsequent referral for secondary cancer care.^22^ In line with published research and guidelines on diagnostic intervals, we will search the patient record for coded symptoms during the year prior to diagnosis for all patients with a cancer diagnosis: 1 year is a trade-off between misattributing unrelated symptoms occurring more than a year before and missing symptoms of relevance by restricting to a shorter period.^22 23^

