### Randomisation and blinding

The eligible practices will be ranked according to their list size from smallest to the largest by the RCGP RSC. These will then be stratified into 10 strata (by list size) such that each strata contains the same number of practices. This is based on the allocation of 10 practices per step. Practices will be randomised in blocks of 10 to the timing of activation of the E-SN toolkit and will crossover in these blocks to the activated phase every 2 months. Therefore, practices will contribute between 2 months and 12 months of E-SN toolkit-activated time (figure 1).

A statistician ([name], Nuffield Department of Primary Care Health Sciences, University of Oxford) who is independent to the intervention development and implementation will produce a stratified randomisation schedule so that within each strata, practices are randomly allocated to each of the six steps, with some replacement practices. The random sequence will be generated using R software. The allocation will be undertaken for all practices at the same time. Where replacement practices are required, these will be taken from the same strata where possible. If no replacement practices from the same strata are available a coin toss will determine whether the next highest or lowest strata will be used to provide replacement practices.

Given the practice change nature of the intervention, clinicians and practice managers will be aware when their practice has switched to the intervention period. Consulting patients providing outcome data will not be informed of the experimental nature of the E-SN toolkit activation and therefore will be blind to the stage of study occurring in the practice they attended. Study personnel involved in extracting outcome data will be blind to the allocated order of the delivery of the intervention across the practices. All data management of extracted data to calculate the outcome measures will be conducted blinded to the timing of switching to intervention. Similar methods have been used in other implementation SW-CRCTs.^26^

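### The headline power for the primary outcome (2 days at 80%) comes from Table 3's most favourable column; with a tail beyond 60 days the detectable difference is about 3 to 9 days, and about 4 for a moderate tail

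*Protocol article*

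**What the plan says.** All references are to the Protocol article.

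- **Headline.** The Sample size section claims: "we would be able to detect an effect size of 2 days with 80% power". The calculation was run in Stata for the Figure 1 layout. The section adds that the main analysis will cover all cancers.
- **Source of the 2 days.** In Table 3 only the first column shows 2 days. It uses a median of 14, a range of 0–60 and 9 cancers per step per cluster. Its label says that it is based on lung cancer.
- **Distribution given in the text.** All cancers: median 5, IQR 0–27. Lung: median 14, IQR 2–45. A further scenario is introduced as "considering primary care intervals towards the 90th centile of 60 days".
- **Outcome window.** The interval starts at the "first recorded symptoms of cancer (within the year prior to diagnosis"), so it can last up to about a year. The Data extraction section says the same.
- **Other Table 3 scenarios with 9 cancers per step.** 5 days (median 14, range 0–100), 13 days (median 60, range 0–365) and 4 days (median 60, range 0–100).
- **Table 3 notes.** For the two columns limited to long delays, the minimum of 14 days is explained as "Minimum set to median of all cancers" or in near-identical words.
- **Design.** The scenarios are "all based on 60 practices, entering in six blocks, with a 12-month preintervention period", and "in each 2-month step, there would be 8–9 cancers per cluster".

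**The concern.** For a difference in mean days, the detectable effect is proportional to the SD, and for a right-skewed interval the upper tail largely sets the SD. The headline column sets its maximum at 60 days. If 60 days is the 90th centile, about one patient in ten lies at or above that assumed maximum, and the outcome definition lets those patients reach 365 days. The lung upper quartile, from the group on which the column is based, is already 45 days.

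The figure at stake is the power for the primary outcome. If 2 days is taken as the trial's resolution, funders and readers will expect an answer on an effect that the design may have well under an even chance of detecting. No column of Table 3 pairs a median of 5 or 14 days with the 0–365 range that the outcome allows, so the table does not show what the full window would do.

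**Working it through.** **Inputs from the protocol.** 60 practices in six blocks of 10; a 12-month pre-period and then six 2-month steps; 9 cancers per practice per step; medians and ranges from Table 3; all-cancer centiles 0 / 5 / 27 (25th, 50th, 75th) and 60 (90th). The text does not name the population of the 60-day centile. It is read here as all cancers.

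**Assumed, because not stated.** Two-sided 5% test; ICC 0 to 0.05; SD from median m and range a to b:

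SD = √{[(a − 2m + b)²/4 + (b − a)²]/12}

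For 14 (0–60): √{[(32)²/4 + 60²]/12} = √(3856/12) = 17.9 days.

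**Standard error.** Stepped-wedge mixed model with fixed period effects and a random practice intercept. At ICC 0 it can be checked by hand. With a share p of practices active, each period contributes 60·p(1 − p). Over p = 1/6 … 6/6 the sum is 60 × (5 + 8 + 9 + 8 + 5 + 0)/36 = 58.3; the pre-period adds nothing. So SE = SD/√(9 × 58.3) = 0.0436 SD. At ICC 0.05, generalised least squares over 6 pre-periods and 6 steps gives 0.0479 SD.

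Detectable difference = (1.960 + 0.842) × SE = **0.122 SD** (ICC 0) to **0.134 SD** (ICC 0.05). With 1 cancer per cell it is 0.367 to 0.376 SD.

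**Step 1: the plan's own figures.**

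| Table 3 column | SD by formula | ICC 0 | ICC 0.05 | Stated |
|---|---|---|---|---|
| 14 (0–60), n = 9 | 17.9 | 2.2 | 2.4 | 2 |
| 14 (0–100), n = 9 | 30.7 | 3.8 | 4.1 | 5 |
| 60 (0–365), n = 9 | 111 | 13.6 | 14.9 | 13 |
| 60 (0–100), n = 9 | 29.0 | 3.5 | 3.9 | 4 |
| 60 (14–100), n = 1 | 24.8 | 9.1 | 9.3 | 9 |
| 60 (14–365), n = 1 | 108 | 39.6 | 40.6 | 39 |

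The headline reproduces to the nearest day. The second column does not reproduce under this formula. An SD of range/4 = 15 also gives about 2 days in column 1 (1.83 at ICC 0, 2.01 at ICC 0.05) but misses the two 365-day columns, so about 18 is the better reading of the SD used.

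**Step 2: the smallest SD that the all-cancer centiles allow.** Put 25% at 0, 25% at 5, 25% at about 15, 15% at 27 and 10% at exactly 60. The mean is 1.25 + 3.75 + 4.05 + 6 = 15.05 and the mean square is 6.25 + 56.25 + 109.35 + 360 = 531.85. SD = √(531.85 − 15.05²) = 17.5. Nobody exceeds 60 days. Spreading patients evenly between the centiles, still with nobody above 60, gives an SD of 21.

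**Step 3: assumed tails above 60 days, same centiles, 9 cancers per step, ICC 0 to 0.05.** Power for 2 days = Φ(2/SE − 1.96), plus a negligible opposite tail.

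| Assumed tail | SD | Detectable difference (days) | Power for 2 days |
|---|---|---|---|
| Nobody above 60, even spread | 21 | 2.6–2.8 | 51–59% |
| Even spread 60 to 100 | 26 | 3.2–3.5 | 36–42% |
| Exponential, continuing the 75th–90th centile hazard (mean excess 33/ln 2.5 = 36 days) | 31.5 | 3.9–4.2 | 26–31% |
| Zero-inflated Weibull, capped at 365 | 33 | 4.0–4.4 | 24–28% |
| Even spread 60 to 365 | 68 | 8.3–9.1 | 9–10% |

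**Step 4: evaluable cancers.** If the 19% diagnosed after emergency presentation have no symptom-to-referral interval, 9 × 0.81 = 7.3 remain per step. The multipliers become 0.136 to 0.148 SD, about 11% larger; at SD 33 this is 4.5–4.9 days.

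**The case against.** **The centiles do not rule out an SD of 18.** A reader might infer that the protocol's own figures contradict its power claim outright. They do not. No SD is stated, 18 is back-calculated, and 17.5 is attainable. The outcome definition permits intervals of a year but does not say how many occur. What stands is that an SD near 18 needs almost no tail, in an outcome defined with a long one.

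**Larger figures are disclosed.** Table 3 prints 5 days for a 0–100 range, plus 4 and 13 days elsewhere. This stands: nothing is hidden, and the defect is the choice of headline. It does not rescue that headline, since the full window is never paired with a median of 5 or 14.

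**The 14 days are declared as lung.** This is true of the first column, and the second is its wider-range variant. Only the two notes on the 14-day minimum conflict with the 5-day all-cancer median in the text.

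**ICC.** It is tempting to infer that the table assumed an ICC of zero. The recalculation does not show this: columns 1, 4 and 5 still round to the stated values at ICC 0.05, only the two 365-day columns point towards zero, and column 2 fits neither. Nor is an unstated SD, ICC or alpha in a condensed article a fault in itself.

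**Evaluable count.** Applying the 19% assumes that the cited figure matches Table 2's definition (diagnosis made before referral). This cannot be checked, and the effect is modest.

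**Analysis scale.** A log-scale analysis in a SAP not shown here would change the calculation, but the claim is stated in days and has to hold in days.

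**Consequence.** It would go too far to say that a null result will be read as excluding 2 days; a reported confidence interval would show what is excluded.

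**Conclusion.** The 2-day claim is a best case presented as the trial's power. It requires an SD of about 15 to 18 days, which is at or near the floor set by the stated centiles. With tails between an end at 100 days and an even spread to 365, the detectable difference is about 3 to 9 days and power for 2 days is roughly 10 to 40%. A moderate tail gives about 4 days, or 4.5 to 4.9 at SD 33 if emergency presentations drop out.

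The range depends on assumptions: the tail shape, the 60-day centile applying to all cancers, ICC 0 to 0.05, a two-sided 5% test and an analysis of mean days. It should not be read as a finding that the true figure is any one of these values. The direction is firm: any patients well beyond 60 days raise the SD, and so the detectable difference, above the headline.

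**What to change.** 1. Replace the 2-day headline with a detectable difference of about 4–5 days at 80% power, shown as a range of about 3–9 days that depends on the assumed distribution. State the SD, ICC and alpha used.
2. Label the 0–60 column of Table 3 a best case, and add a scenario based on the all-cancer centiles with the full 0–365 window.
3. Correct the two notes that treat 14 days as the all-cancer median; the text gives 5.
4. Re-estimate the SD, the ICC and the number of cancers with a calculable interval from the extraction already planned at the start of the stepped wedge. By the protocol's own count it covers about 60 × 53 = 3,180 cancers in the 12 months before activation, and it carries no information on the intervention effect.

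Cost: wording and a less favourable stated figure. The number of practices, the outcome and the analysis are unchanged.

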### Statistical analysis

In patients with a diagnosis of cancer, we will calculate the primary outcome of primary care interval (time between first recorded symptom and referral), proportion diagnosed after emergency presentation and the recorded diagnosis. Among consulting patients, we will calculate the rate of direct access cancer investigation and rates of referrals via 2 weeks wait, urgent and routine pathways, as well as the number of consultations during the primary care interval, and the template activation rate. A patient referred to: a 2-week wait pathway will be reviewed by a specialist within 2 weeks; an urgent pathway will be reviewed as a priority but the exact timing varies between specialty and healthcare setting; a routine pathway requires specialist review but on a non-urgent basis.

Regarding the analysis of the stepped-wedge design and the effect of correlation of observations within clusters, will model the association using a fixed effect for the intervention condition of the cluster at each time step, a fixed effect for time and other covariates (eg, changes in cancer guidelines), and then include a random effect for practice and a random effect for patient to account for correlation of the observations from the same centre and from the same participant.

Analyses will include all patients registered at participating practices. Practices that withdraw their agreement to participate will be included in analyses up to the point of withdrawal, unless they indicate that they wish to withdraw previously collected data from analysis.

Our primary analysis will be carried out on an intention to treat principle. Therefore, if any practice does not switch on the E-SN toolkit at the correct time for their cluster, we will carry out the analysis under the assumption that the E-SN toolkit was switched on at the correct time.

The primary care interval is defined from the presence of symptoms and referral in the primary care record. Symptoms of interest will include all symptoms included in the urgent referral guidelines including vague symptoms such as weight loss, tiredness and back pain.^35 36^ Missing data for these variables in the record will be interpreted as the absence of symptoms or referral, respectively. Extracted data from the primary care record will be limited to the study period plus the preceding year, so symptoms recorded prior to this will not be visible to the research team.

The study will not have a formal data monitoring committee as patients will be receiving standard care through their GP, and all data will be extracted from routinely collected clinical notes.

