An electronic safety-netting toolkit (E-SN toolkit) has been developed through consultation with GPs in the UK and was embedded within one of the major clinical systems in England—Egerton Medical Information System (EMIS) Web in May 2018. The toolkit is designed to replace existing verbal or paper methods of safety netting by providing effective means for tracking and follow up by administrative staff. The E-SN toolkit proposes a rigorous, robust, traceable and auditable proactive approach to tracking patients. It is designed to allow clinical data to be entered using templates, and diary entries to be generated (time reminders to check an action has been completed). Using diary entries, users can effectively follow up test requests, referrals and non-specific but concerning symptoms. For instance, outstanding actions appear as ‘Alert Flags’ to identify incomplete diary entries and can be collated. Although the E-SN toolkit is currently available to general practices using EMIS, practices have to proactively turn it on to implement it in their current practice.

This study aims to evaluate the effectiveness of an EHR safety-netting toolkit (E-SN toolkit) for use in primary care with patients with symptoms of cancer.

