Key Secondary Outcomes	Proportion of cancers diagnosed after emergency presentation measured during inactive and active E-SN phases. Recorded new diagnoses in those who have a template activated, measured by cancer site and stage, and by non-cancer diagnosis, during the active E-SN stage. Total time to diagnosis measured from first recorded symptom to definitive diagnosis for all cancer diagnoses during the inactive and active E-SN phases and all diagnoses with template activation during the active E-SN phase No of GP consultations/patient between first record of symptom and cancer referral, measured during the inactive and active E-SN phase Rates of patients completing direct access cancer investigations measured during the inactive and active E-SN phase Rates of patients referred measured as 2-week wait, urgent, and routine, during the inactive and active E-SN phase Timing of template activation within the primary care interval (from first symptom to referral) measured during the active E-SN phase Template activation rate among consulting patients, both total and stratified by individual GP, measured during the active E-SN phase The proportion of diary entries completed measured during the active E-SN phase The reason for template activation measured based on 20 high-level READ codes during the active E-SN phase Symptoms leading to direct access to investigations measured during the active E-SN phase Recorded vague symptoms in the template measured during the active E-SN phase Demographic details of patients with activated templates measured during the active E-SN phase GP type completing template (eg, partner, locum, trainee) measured during the active E-SN phase Diagnostic codes in patients with activated templates measured during the active E-SN phase

EMIS, Egerton Medical Information System; E-SN, electronic safety-netting; GP, general practitioner.

The anticipated length of the study is 18 months. This consists of 3 months recruitment, followed by a 12-month period during which time the intervention will be introduced, and 3 months for analysis.

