**Figure 2 F2:**
[figure not shown]
Diagram showing the definitions of time-based outcomes.

**Table 2 T2:** Outcomes, measures and time periods of measurement for primary and secondary outcomes

Outcome	Measure	Inactive study period	Active study period	Template activations only
Primary outcome				
Primary care interval for cancer diagnoses	Measured as the no of days between first recorded symptoms of cancer (within the year prior to diagnosis) and subsequent referral for secondary cancer care	X	X	
Secondary outcomes				
Proportion of cancers diagnosed after emergency presentation	Proportion of cancers for which diagnosis is made prior to referral, including following A&E or inpatient episodes. Where there is uncertainty regarding the route of diagnosis, the RCGP RSC network will contact the practice in an attempt to augment the data. Algorithms will also be developed to identify emergency presentations of cancer.	X	X	
Recorded new diagnoses in those who have a template activated	By cancer site and stage, and non-cancer diagnoses. Coded entries for all alternative diagnoses where the E-SN toolkit has been activated will be identified.		X	X
Total time to diagnosis (from first recorded symptom to definitive diagnosis)	Measured from first recorded symptom of cancer (within the previous year) to definitive diagnosis for all cancers diagnosed, and for all patients with an activated template	X	X	X (for non-cancer diagnoses)
No of GP consultations/patient between first record of symptom and cancer referral	Measured as no of primary care consultations between the first recorded symptoms (within the year prior to diagnosis) and subsequent referral, per patient.	X	X	
Rates of patients completing direct access cancer investigations	Measured as the no of patients undergoing direct access cancer investigations (according to those specified in referral guidelines NG12) in each period divided by the person years of observation for that period.	X	X	
Rates of patients referred for cancer	Referrals rates via 2-week wait, urgent, and routine routes for all patients referred for specialist opinion to a secondary care cancer specialist	X	X	
Timing of template activation	Measured as the no of days between first recorded symptoms (within the year prior to diagnosis), and template activation and the no of days between template activation and subsequent referral.		X	X

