Template activation rate among consulting patients	Measured as the number of patients with an activated template divided by the no of patients consulting, in each time period. Both total rate and rate stratified by individual GP will be measured.		X	X
Proportion of diary entries that were completed	Measured as the no of diary entries that were completed divided by the number of diary entries that were opened.		X	X
Reason for template activation	The coded reasons for activating the template, Based on 20 high level READ codes		X	X
Symptoms leading to direct access to investigation	All symptoms recorded in patients undergoing direct access cancer investigations	X	X	
Recorded vague symptoms in the template	All symptoms recorded within the template.		X	X
Demographic details of patients with activated templates	Age and sex of patients that had a template activated during the course of the trial.		X	X
GP type completing templates	Descriptive data on the type of GP that first activated the template (eg, partner, locum, trainee)		X	X
Diagnostic codes in patients with activated templates	Diagnoses recorded after the activation of template.		X	X

E-SN, electronic safety-netting; GP, general practitioner; RSC, Research and Surveillance Centre; RSC, Research and Surveillance Centre.

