### Cancer diagnosis in the time of COVID-19

The COVID-19 pandemic has led to considerable changes in general practice, including a switch from predominantly face-to-face consultations to remote consultations by telephone or video call. In addition, many non-urgent hospital outpatient consultations and investigations have been cancelled or delayed, and it is likely that patients are less willing to consult with clinicians for what they perceive as ‘minor’ conditions, due to a desire to reduce pressure on the health service. All of these factors are likely to impact on cancer diagnosis and referral.

As a result, the initiation of the CASNET2 study has been delayed in an attempt to minimise the effect of these factors on the results of the study, and to ensure that the results are generalisable. However, we also intend to carry out supplementary downloads from participating practices for the 12 months prior to March 2020 (baseline comparison period) and for the entire pandemic period, or until 31 October 2020, whichever is latest.

We will then conduct a before-and-after analysis of the following outcomes:

Presenting symptoms of cancer.Primary care interval for cancer diagnosis.Proportion of cancers detected after emergency presentation.Site and stage of new cancersTotal time to diagnosis.Number of consultations in primary care interval.Rates of patients completing direct access cancer investigations.Rates of patients referred by 2-week wait, urgent and routine routes.

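### The direct-access investigation rate is given two different bases, the referral rates have none in Table 2, and the consulting-patient basis could be affected by the toolkit

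*Protocol article*

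**What the plan says.** The Statistical analysis section of the protocol article sorts outcomes by population. A first group is calculated in patients with a cancer diagnosis. It then continues: "Among consulting patients, we will calculate the rate of direct access cancer investigation and rates of referrals" by the three referral routes, and adds to the same list the number of consultations in the primary care interval and the template activation rate. Later the section states: "Analyses will include all patients registered at participating practices".

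Table 2, to which the Secondary outcomes section refers for full details, is laid out differently:

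- **Direct access investigations:** the number of patients investigated "in each period divided by the person years of observation for that period".
- **Referrals:** "Referrals rates via 2-week wait, urgent, and routine routes for all patients referred for specialist opinion to a secondary care cancer specialist". This describes who is counted as referred, but not what the count is divided by.
- **Template activation:** patients with an activated template "divided by the no of patients consulting, in each time period". This is the one rate for which Table 2 uses consulting patients, and it is measured in the active period only.

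Table 1 makes the investigation rate a between-phase comparison: "Rates of patients completing direct access cancer investigations measured during the inactive and active E-SN phase". It treats the referral rates in the same way. The Abstract names both among the other outcomes.

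**The concern.** An analyst who follows Table 2 and one who follows the Statistical analysis text would compute different quantities for the investigation rate, and nothing in the article says which governs. For referrals, the only outcome-specific basis is the consulting-patient one, and it conflicts with the general statement about registered patients.

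The choice matters because these rates are compared between inactive and active phases. Whether a patient consults in a given two-month period is observed after activation, and the toolkit can plausibly influence it. The Background says: "Using diary entries, users can effectively follow up test requests, referrals and non-specific but concerning symptoms". The Intervention section adds that expired diary entries are searched for and acted on, and that low-risk patients are monitored. If some of these patients are recalled in a later period when they would not otherwise have consulted, they enter the denominator because of the intervention. The per-consulter rate could then move without any change in referrals or tests.

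**Working it through.** The article gives no rate, power figure or sample size for these two outcomes, so there is no stated figure to reproduce. The check has two parts.

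**1. The passages side by side**

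| Outcome | Table 2 | Statistical analysis |
|---|---|---|
| Direct access investigation rate | person-years of observation | consulting patients |
| Referral rates (three routes) | no denominator stated | consulting patients |
| Template activation rate | patients consulting | consulting patients |
| Consultations in the primary care interval | per patient, from first symptom in the year before diagnosis to referral | listed under consulting patients |
| Analyses in general | – | all registered patients |

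Only the template activation row agrees. The investigation row conflicts outright. The referral row is undefined in Table 2. The consultation count is tied by Table 2 to patients with a diagnosis, so it belongs with the cancer-patient outcomes.

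**2. Sensitivity of the active-versus-inactive ratio to the denominator**

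Let RR be the true rate ratio per registered person-time, and let x be the relative change that activation causes in the number of distinct patients consulting in a period. Then

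RR per consulting patient = RR / (1 + x).

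The baseline share of patients who consult cancels. The person-time ratio does not contain x. The documents give no value for x, so the values below are assumptions.

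| x (assumed) | True RR 1.00 shown as | True RR 1.10 shown as |
|---|---|---|
| −5% | 1/0.95 = 1.053 | 1.10/0.95 = 1.158 |
| 0 | 1.00 | 1.10 |
| +2% | 1/1.02 = 0.980 | 1.10/1.02 = 1.078 |
| +5% | 1/1.05 = 0.952 | 1.10/1.05 = 1.048 |
| +10% | 1/1.10 = 0.909 | 1.10/1.10 = 1.00 |

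With unchanged numerators, +5% gives 0.952 − 1 = −4.8% and +10% gives 0.909 − 1 = −9.1%. At +10%, a true 10% increase would show as no effect. At x = 0 the two bases give the same ratio.

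**The case against.** The best defence is that Table 2 is the designated definition and that the phrase about consulting patients is a loose label, separating whole-population outcomes from those confined to cancer patients. The inclusion of the consultation count, which cannot sensibly use that denominator, supports this. The reading is possible but weak. The same list contains the template activation rate, for which consulting patients is the actual denominator, so the phrase is operative for at least one item. Nothing tells the analyst for which items it is not.

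Several stronger readings are tempting and are not supported:

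- **That both outcomes have two stated denominators.** This holds only for investigations. Table 2 states none for referrals.
- **That extra follow-up visits lower the rate.** The consulting denominator in Table 2 counts patients per period. A repeat visit by a patient already counted adds nothing; only a distinct patient who would not otherwise have consulted in that period does.
- **That every toolkit feature exists to bring patients back.** The article describes tracking by administrative staff, and in its own example the entry is closed when the result returns, with no further consultation mentioned. Recall is plausible for some patients, not a stated purpose of each function.
- **That 5% to 10% is an expected effect.** It has no anchor in the article. On a list of about 10 000, if 20% to 50% consult in a two-month step (assumption), there are 2 000 to 5 000 consulters. A 5% rise then means 100 to 250 additional distinct patients per practice per step, and 10% means 200 to 500. That is a lot for templates used at clinicians' discretion.
- **That the COVID-19 section supports the bias.** Its remark that "it is likely that patients are less willing to consult with clinicians" concerns pandemic behaviour and a separate before-and-after analysis, not an effect of the toolkit. In the main model, calendar changes common to practices are addressed by the fixed time effect.

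What stands is that the bias is conditional. The conflict between the passages is not.

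**Conclusion.** The point holds in limited form. For direct access investigations, the article fixes two different bases. For referrals, Table 2 leaves the basis unstated, and the Statistical analysis section supplies only one that conflicts with its own registered-patient sentence. Following that section as written gives a different estimand from Table 2 for an active-versus-inactive comparison, conditioned on a status that the intervention can affect.

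Whether this produces bias depends on activation changing the number or mix of distinct patients who consult. The article gives no information on that, so neither direction nor size is known. The percentages shown only indicate sensitivity: they assume unchanged numerators and include zero when consulting does not change. These are secondary outcomes. The primary outcome, the sample size and the randomisation are not affected.

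**What to change.** - In the Statistical analysis section, and in the referral row of Table 2, state registered adult person-years per practice-period as the denominator for the direct access investigation rate and for all three referral-route rates.
- Keep consulting patients as the denominator for the template activation rate. Any per-consulter version of the other rates should be labelled descriptive or a sensitivity analysis.
- List the number of consultations in the primary care interval under patients with a cancer diagnosis, as Table 2 implies.

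The form of the model can be left to the SAP. The cost is wording only: Table 2 already requires person-years for the investigation rate, and the Data extraction section already covers all registered adults who have not opted out.
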